
### 2.9. Data Collection Method

The study employs a hybrid data collection strategy to clearly separate the educational game mechanics from the research evaluation process. All formal assessments related to the study outcomes—including sociodemographic data, the PPDS, and the knowledge tests—will be administered exclusively in physical paper format. This ensures that research data collection does not depend on the stability of the digital platform during the session. Google Forms will be used solely as a functional component of the gamification (acting as “digital locks”). Participants enter their clinical answers into these forms to obtain the passwords required to advance through the Wix narrative. These digital responses serve an instructional purpose and are not the primary source for academic performance analysis.

To ensure high-quality data and minimize errors during the transition from paper to digital analysis, each student will be assigned a unique alphanumeric code on their first paper form (Form 0), which must be manually transcribed by the student onto all subsequent paper assessments (Forms 1F to 4F) to enable longitudinal matching. The PI will manually enter the data from the paper forms into a pre-configured offline database. To promote data integrity, a random 10% sample of the paper forms will be cross-checked against the digital database by a co-author to ensure transcription accuracy.

The primary strategy for participant retention is the integration of the trial into the mandatory face-to-face academic calendar. The educational value of the simulations as preparation for the final exam serves as the main incentive for completion. Reasons for any missing sessions or incomplete paper forms will be recorded in the field diary to be reported as feasibility outcomes.

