## Abstract

**Background/Objectives**: Simulation-based education often lacks personalization, focusing on technical competence rather than individual student profiles. This protocol describes a study designed to evaluate whether adapting gamified narratives to nursing students’ personality profiles has the potential to support academic performance in obstetrics. This study aims to validate the integration of psychometric profiling and AI as a sustainable strategy for personalized clinical training. **Methods**: A cluster-randomized controlled longitudinal pilot trial will be conducted at the University of Atlántico Medio. The protocol has been submitted for registration at ClinicalTrials.gov (Registration Pending). Thirty-eight second-year nursing students meeting inclusion criteria (excluding repeaters or those with prior specialized training) will be assigned by natural practice to either a control group (generic gamification) or an experimental group (gamification adapted according to Player Personality and Dynamics Scale profiles using AI-generated content). The intervention comprises four clinical simulation sessions focusing on pregnancy and childbirth, which are managed via the Wix platform. The primary outcome is academic performance, measured as “Learning Gain” (post-test scores minus pre-test scores). Secondary outcomes include student satisfaction measured via the Gameful Experience Scale. Data will be analyzed using Mann–Whitney U tests to compare overall efficacy and intragroup evolution. To minimize observer bias, knowledge assessments will utilize automated, objective scoring, and participants will be blinded to the study hypothesis. **Expected Outcomes**: The study aims to establish the technical and pedagogical feasibility of integrating AI-adapted narratives into nursing curricula. It is anticipated that the personalized approach will show positive trends in learning gains and engagement patterns, providing a baseline for larger multicenter trials. **Conclusions**: This protocol presents a framework for “Precision Education” in nursing, shifting from “one-size-fits-all” simulations to student-centered adaptive training. The use of Generative AI makes such personalization sustainable and cost-effective for health science faculties.

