### 2.5. Randomization and Masking

Given the nature of practical teaching (in which groups are pre-established by enrollment), simple individual randomization is not possible. Therefore, a cluster randomization design will be implemented. An independent researcher not involved in the teaching process will use (RANDOM.ORG; Randomness and Integrity Services Ltd., Dublin, Ireland) computerized random number generation software to assign the practice shifts (clusters) to either the CG or EG arm. Allocation concealment is ensured as the assignment will only be revealed to the Principal Investigator and students on the first day of the intervention.

Given the highly experiential nature of the intervention, participant blinding to the educational differences between conditions is likely only partial. However, participants will remain naive to the comparative study hypothesis and their specific allocation to either the control or experimental cohort. However, due to the logistical requirements of the intervention (the distribution of specific login codes), the Principal Investigator (PI) cannot be blinded during the sessions. To mitigate bias and ensure external control, statistical data analysis will not be performed by the PI. Instead, it will be performed by a different researcher (the co-author) who was not involved in the teaching process, using a dataset in which the group assignment is masked (coded as Group A vs. Group B).

To maintain this blinding and prevent the participants from distinguishing between the narrative formats (generic vs. adapted), the intervention relies on the physical and temporal separation of the clusters. Since Group A and Group B attend consecutive but distinct shifts, there is no simultaneous visual contact with the screens of the Control and Experimental groups. Furthermore, the clinical content and the structure of the Google Forms (Google LLC, Mountain View, CA, USA) remain visually identical for both groups; only the Wix interface ‘wrapping’ differs, and this is not visible to the other group due to the shift separation.

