The total cohort of 38 students will be divided into two consecutive practice shifts (Group A and Group B): one with 18 students and the other with 20. In the first session, software will be used to randomly assign which group will have the first shift. Students will remain in their assigned group for all four sessions to avoid cross-contamination. The program consists of four compulsory thematic modules:-Session 1: Prenatal care;-Session 2: Maternal-fetal assessment and well-being;-Session 3: Obstetric risk triage;-Session 4: Critical management in pregnancy.

Each day of the internship follows the same 120 min (2 h) time structure, which is visually summarized in Figure 2.

During the middle 60 min (intervention), the PI will monitor activity as the students interact with their devices. In the CG, all learners receive the same login URL and password, and the storytelling in Wix is standard. The mechanics are the same for everyone: progress bars are present, and points are awarded for correct answers. In the EG (PPDS-Adapted Gamification), at the beginning of each session, the PI provides differentiated codes (according to role) based on the learner’s profile to access five parallel narratives in Wix for the same clinical case. The clinical goal is the same for all participants, but the narrative “wrapping” and side mission change.

To ensure fidelity, the PI will be the only person with admin privileges in Wix and access to the Google Forms answers in real-time. Attendance will be monitored using signatures. The PI will resolve technical or clinical questions during the session, ensuring that the password lock in Wix does not impede the progress of learning.

Forms will be set up as “required steps” within the Wix narrative. In the case of the EG, the knowledge forms will be identical in content but esthetically matched to the identified player’s profile.

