As the researcher is also the teacher who evaluates the coursework, this could introduce unconscious bias (Pygmalion Effect) to favor the EG or generate in the students a desire to please the teacher by responding positively to the surveys. To address this situation, the knowledge-assessing questionnaires contain multiple-choice questions to facilitate automatic and objective correction and eliminate subjectivity on behalf of the evaluator. Anonymity will be guaranteed for the satisfaction surveys to encourage honesty.

As for the profile self-evaluation through the PPDS, the classification of the students depends on their sincerity when answering the test. It may be that a “Toxic” student does not recognize themselves as such and marks “Coacher” answers due to social desirability, thus being assigned a narrative that does not correspond accurately to their profile. This issue will be addressed by clearly explaining that there are no “good or bad” profiles, thus reducing social pressure.

Another limiting aspect is the risk of contamination between groups. As students are classmates from the same faculty, the CG students may learn about the existence of the EG’s “special missions” and feel demotivated (demoralizing effect) or try to obtain the EG passwords. To address this issue, Wix login passwords will be changed on a per-session and group basis, and explicit confidentiality will be required as part of the “game contract”. To actively monitor this risk without increasing survey fatigue, the Principal Investigator will utilize the pre-established “field diary” to record any spontaneous student disclosures or observable evidence of cross-contamination between the shifts. Any detected contamination will be reported as a feasibility metric and factored into the interpretation of the exploratory efficacy results. While this observational approach is suitable for a pilot, future definitive trials will benefit from incorporating a formal self-report question to empirically measure cross-contamination rates.

Finally, as a logistical limitation, and given the nature of the study, failures in the faculty’s Wi-Fi connection, Wix server crashes, or problems with students’ mobile devices could interrupt the intervention. An alternative plan will be available, with changes in the teaching schedule agreed upon with the students so that a new practical session may be scheduled.

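### The automated scoring offered against observer bias does not cover the step at which the unblinded teacher-PI types in the paper primary-outcome tests, and two sections conflict on how the forms look

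*Protocol article*

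**What the plan says.** On scoring, the Abstract says that "knowledge assessments will utilize automated, objective scoring" and gives this as a measure against observer bias. Section 4.1 raises the possibility that the teacher-researcher unconsciously favors the experimental group (EG). It answers that the questionnaires are multiple choice "to facilitate automatic and objective correction and eliminate subjectivity on behalf of the evaluator".

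On data handling, Section 2.9 says that "the PPDS, and the knowledge tests—will be administered exclusively in physical paper format". It confines Google Forms to the digital locks of the game and says that their responses are not the main source for academic performance. It continues: "The PI will manually enter the data from the paper forms into a pre-configured offline database". The control on this step is that "a random 10% sample of the paper forms will be cross-checked against the digital database by a co-author to ensure transcription accuracy". No error threshold and no follow-up action are given.

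On the PI's position, Section 2.5 says the PI cannot be blinded during the sessions. Section 2.7 has the PI lead all sessions and hand out the profile-specific codes in the EG. Section 2.8 says the PI designed the test and is the lecturer in charge. Section 2.11 gives the PI sole custody of the link between code and identity.

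On appearance, Section 2.5 says that the clinical content and the structure of the Google Forms "remain visually identical for both groups". Section 2.7 says that in the EG "the knowledge forms will be identical in content but esthetically matched to the identified" player's profile, and that forms are set up as required steps inside the Wix narrative.

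Section 2.10 says that the article is the full protocol and analysis plan and that no separate plan exists.

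**The concern.** A safeguard against observer bias has to cover every step at which someone who knows the arm can affect the outcome value. Automated scoring removes judgement in marking. It does not remove the step in which answers go from paper into the database, and the person given that step knows every student's arm, wrote the test and teaches both groups. Masking the analyst cannot help here, because the values already exist when the masked dataset is made. Section 2.11 delays the analysis until transcripts are locked, but it says nothing about who handles the entries or when.

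The pilot's stated statistical purpose is to estimate an effect size and a variance for later trials (Sections 2.4 and 2.10). Any distortion at entry would carry into those estimates. The conflict over form appearance also leaves a reader unsure whether the same instrument is used in both arms.

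**Working it through.** **Comparison of the passages on scoring and entry.** The protocol gives no figure to reproduce on this point, so the check is mainly textual.

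1. Automated scoring is claimed for the knowledge assessments (Abstract) and offered as the remedy for PI bias (Section 4.1).
2. The knowledge tests are on paper only, and the PI enters them by hand (Section 2.9).
3. The only tool described as checking answers by itself is Google Forms (Section 2.7), and Section 2.9 rules it out as the main outcome source.
4. No section describes how entered paper answers are turned into a score. The pre-configured database might do this, but the text does not say so.
5. The analyst receives a dataset coded Group A and Group B (Section 2.5), which comes after step 2.

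The safeguards in steps 1 and 5 therefore lie on either side of the entry step without covering it.

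**Comparison of the passages on appearance.** If the knowledge forms of Section 2.7 are the on-screen Google Forms, matching them to the profile contradicts Section 2.5. If they are the outcome tests, placing them inside Wix contradicts Section 2.9. The wording needs reconciling on either reading.

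**How strong is the 10% check?** Assume all 38 students consent and attend, with five paper forms each (Form 0 and Forms 1F to 4F): 38 × 5 = 190 forms, of which 19 are checked and 171 are not. With k faulty forms, the chance that the sample contains at least one is 1 − C(190 − k, 19) / C(190, 19):

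- k = 1: 0.10
- k = 3: 0.27
- k = 5: 0.41
- k = 10: 0.66
- k = 19: 0.88

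About 27 faulty forms (27/190 = 14%) are needed before detection reaches 95%. Counting only Forms 1F to 4F gives 38 × 4 = 152 forms with 15 checked. The detection chances are almost the same, and again 27 faulty forms (18%) are needed.

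**How far would a keying error move the result?** The number of items per post-test is not given. Section 2.8 gives a 40-item questionnaire covering four cases, so 10 items per session is assumed, with 40 per session as the other end of the range.

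- 10 items: one wrong item moves the session score by 10/10 = 1 point and the student's four-session mean by 1/4 = 0.25. The arm mean moves by 0.25/20 = 0.0125 or 0.25/18 = 0.0139.
- 40 items: the session score moves by 10/40 = 0.25 and the student's mean by 0.25/4 = 0.0625. The arm mean moves by 0.0625/20 = 0.003 or 0.0625/18 = 0.003.
- Ten errors, all in one arm and all in the same direction, at 10 items per session: 10 × 0.0125 = 0.125 to 10 × 0.0139 = 0.139 points on the 0–10 scale. Five such errors: 0.06 to 0.07.

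**The case against.** The best defense is that manual entry and automated scoring are compatible. The PI may simply key the chosen option, after which the database compares it with a fixed key. Multiple-choice answers leave little to judge, the paper originals allow a check, and a random sample is checked. Honest slips have no reason to favor one arm, and the primary test uses ranks. Sections 2.4, 2.10 and 4.1 call the efficacy comparison exploratory, the dual role is openly acknowledged, and with one cluster per arm confounding by cluster is a far larger threat than keying.

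Much of this stands. A reader might infer that the safeguard does not exist at all, or that hand entry contradicts automated scoring. The documents do not support that: the scoring step is undescribed, not excluded. A reader might also infer that the outcome tests look different in the two arms. The sentence in Section 2.7 directly follows one about required steps inside Wix, so it most naturally refers to the on-screen locks, and Section 2.7 also says the multiple-choice questions are identical in both groups. Finally, the detection figures might be read as evidence of material bias. They show only that the check is weak against a few faults.

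What the defense does not answer is that, even with a fixed key, the input to that key is typed by an unblinded person with a stake in the result.

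**Conclusion.** The point holds in a limited form. The protocol's stated protection against observer bias does not extend to the entry of the primary-outcome tests, and no automated scoring of paper tests is described. The 10% check would miss five faulty forms with probability 0.59 and ten with probability 0.34, taking 190 forms. The likely effect of honest errors is nevertheless small, at roughly 0.003 to 0.014 points on an arm mean per wrong item, depending on the assumed test length. A shift that mattered would need many errors in the same direction. The reason to act is that unblinded handling of the outcome is easily avoided, not that a bias has been shown.

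Sections 2.5 and 2.7 conflict on form appearance. This is probably a matter of wording about the digital locks, but as written it leaves open whether the outcome instrument is the same in both arms.

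**What to change.** - Have a non-teaching co-author enter the item-level answers from paper tests that carry only the student code and no arm label. Section 2.9 already gives a co-author the 10% check, and Section 2.5 already has one outside the teaching. The text does not say whether they are the same person, so this should be stated.
- Score the entered answers with a fixed key, in the database or by script, and describe this step in Section 2.9.
- State that the PI does not enter or change outcome data, and that any verification of entries is made against the paper originals.
- State that the paper tests are identical in both arms, and limit any visual matching to the digital locks.
- Bring the Abstract and Sections 2.5, 2.7, 2.9 and 4.1 into line, so that the claim of automated scoring describes what will be done.

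The cost is a few hours of an existing co-author's time for up to about 190 short forms, plus wording. Full double entry would give more assurance but needs a second person whom the protocol does not name. It is not necessary for an exploratory pilot of this size.

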### 2.10. Data Analysis

This publication constitutes the full trial protocol and detailed statistical analysis plan. No separate analysis plan document exists. Any future deviations from this plan will be reported and justified in the final results publication.

Data analysis will be carried out using the Jamovi 2.6.44 statistical package (The jamovi project, Sydney, Australia). Statistical significance level of *p* < 0.05 will be established; however, given the exploratory nature of these analyses, we will rely less strongly on *p*-values and give greater importance to effect sizes and 95% confidence intervals. In addition to statistical significance testing, the effect size and 95% confidence intervals will be reported for all primary outcomes. This approach prioritizes the estimation of the magnitude of the intervention effect, which is the primary statistical goal of this pilot study.

Before inferential analysis, the raw variables extracted from the forms 1F to 4F will be processed to generate the result metrics. The absolute LG will be calculated using the following formula: (PostTestScore) − (PreTestScore). To facilitate comparison, raw scores will be normalized to a standard grading scale of 0 to 10 points. This calculation will be applied consistently across all four sessions. To handle missing data, given the compulsory attendance requirement, a complete-case analysis approach will be utilized; participants with incomplete data for a session will be excluded from that specific analysis. Consequently, if a participant misses a session, their global LG metric will be calculated as the mean of their completed sessions only.

To handle the repeated measures design within the constraints of the pilot sample size, the primary analysis will not utilize complex mixed-model ANOVAs. Instead, the LG scores from the four sessions will be averaged to generate a global LG metric for each student. This summary measure is educationally meaningful as it reflects the overall assimilation of the obstetric module, mitigating the impact of performance fluctuations in any single session. This aggregation strategy aims to reduce intra-individual variance and provide a more robust estimator for the main group comparison. The normality of the dependent variables will be evaluated using the Shapiro–Wilk test. Given the estimated sample size, the use of non-parametric statistics is assumed to be a priority, unless the data demonstrates a normal distribution.

A descriptive analysis of sociodemographic data and previous experience will be carried out, qualitative variables will be presented as absolute and relative frequencies, and quantitative variables will be presented as medians and interquartile ranges (if the distribution is not normal) or means and standard deviations if the distribution is normal.

To compare the overall efficacy (CG versus EG), the homogeneity at baseline will be checked. The Pre-test (Form 0) scores and the average grades according to academic records will be compared between both groups using the Mann–Whitney U test to ensure that the groups are comparable despite the cluster randomization. Additionally, prior gamification exposure and the distribution of PPDS profiles will be descriptively compared at baseline to identify any major initial imbalances between the clusters

To test the primary hypothesis, the mean global LG of the four sessions between the CG and the EG will be compared using the Mann–Whitney U test for independent samples. Given that the study design involves two natural clusters of unequal size (n = 18 and n = 20), the main hypothesis test will be performed at the participant level. Given the limitation of having only one cluster per arm, inferential statistics will be considered strictly exploratory, and results must be interpreted with caution.

Regarding the secondary outcomes, the analysis of the five PPDS profiles will be strictly descriptive and exploratory, given the limited sample size. Subdividing the experimental group (n = 20) into five profile categories yields cell sizes too small for robust inferential statistics; hence this approach prioritizes statistical rigor by avoiding underpowered hypothesis testing on these specific sub-variables.

To analyze the students’ perception at the end of the study, the satisfaction scores (GAMEX) will be compared between groups using the Mann–Whitney U test. Finally, an exploratory Spearman correlation analysis will be performed between satisfaction and LG to determine if the students who enjoyed the experience the most were also those who learned the most.

Additionally, exploratory analyses will be conducted to examine the potential influence of sociodemographic factors on the intervention outcomes. Spearman’s rank correlations will be used to assess the relationship between age, prior academic grades, and the global LG. Gender differences regarding performance and satisfaction will also be descriptively explored. However, due to the limited pilot sample size, these specific sociodemographic subgroup analyses will be treated strictly as hypothesis-generating.

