### 2.8. Outcome Variables

The main outcome variable will be academic performance, LG, understood to reflect new knowledge acquired on the subject under study. The degree of assimilation of the theoretical and practical concepts of pregnancy and childbirth in each of the four clinical cases will be evaluated. To this aim, an “ad hoc” questionnaire comprising 40 multiple-choice questions was designed by the PI, who is a certified Nurse Specialist in Obstetrics and Gynecology (Midwife) and the lecturer in charge of the class. The items were constructed to strictly align with the specific curricular contents and learning objectives of the ‘Reproductive Health’ syllabus. To ensure external content validity prior to administration, this initial draft will be reviewed by an external panel of five experts (three academic midwives and two obstetricians). Regarding reliability, since this is a pilot study, internal consistency and item analysis will be calculated post hoc to validate the instrument for future trials. The questions in the final questionnaires (administered post-simulation at each session) will address the same content as the initial questionnaire, but the form and order of the answers will be modified. Learning gain will be calculated using a simple difference (post-test score minus pre-test score), normalizing the results on a scale of 0 to 10 points. An arithmetic mean of the learning gain scores obtained from the four use cases will be calculated.

The secondary outcome variables will be

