### 4.1. Limitations

A methodological limitation that is worth highlighting is the size of the sample, which is limited by the official ratio of students per internship group and could reduce the statistical power of the study, making it difficult to detect significant small differences between subgroups. To mitigate this issue, the use of non-parametric tests will be prioritized. In addition, the study is planned as a pilot, whose main objective is to validate the statistical trend and effect size for future multicenter trials.

Regarding the randomization of entire natural groups rather than individuals, there is a risk that the groups may not be entirely homogeneous at baseline. Specifically, having only one cluster per arm constitutes a major design limitation, as the intervention effect may be confounded with cluster-level differences. Therefore, any efficacy comparisons between groups in this pilot phase are strictly exploratory. To address this, a strict statistical verification of comparability will be conducted. If significant baseline differences are detected, they will be explicitly reported and considered potential confounding variables during the interpretation of results, acknowledging that parametric adjustment methods may not be applicable given the sample size constraints.

It is important to acknowledge that the assessment of academic performance acquisition in this study is restricted to the cognitive domain (knowledge and theoretical decision-making), which will be measured via written tests. Due to the pilot nature of the study and logistical constraints, objective measures of psychomotor clinical competence or behavioral transfer to practice, such as Objective Structured Clinical Examinations or checklists in high-fidelity environments, will not be included. Future phases of this project will aim to incorporate these practical dimensions to evaluate the ‘transfer of training’ to the bedside.

It should be noted that there may be a “Novelty Effect” and the improvement in initial performance may simply be due to the novelty of using technology (Wix) in class and not to the specific narrative adaptation. The longitudinal design of four sessions (spanning four consecutive weeks) will help to dilute this effect. By monitoring the students over a one-month period, which corresponds to the ‘first few weeks’ where initial motivation typically decreases, we can determine if engagement is maintained until the final session.

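### Baseline handling rests on a low-powered significance check, and sample size is not a valid reason to omit a Form 0-adjusted estimate beside the gain-score comparison

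*Protocol article*

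**What the plan says.** All references are to the protocol article.

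- **Outcome (Section 2.8).** "Learning gain will be calculated using a simple difference (post-test score minus pre-test score), normalizing the results on a scale of 0 to 10 points". The session gains are then averaged into one global LG per student.
- **Primary comparison (Section 2.10).** "the mean global LG of the four sessions between the CG and the EG will be compared using the Mann–Whitney U test". No covariate enters.
- **Baseline check (Section 2.10).** "The Pre-test (Form 0) scores and the average grades according to academic records will be compared between both groups using the Mann–Whitney U test". The stated purpose is "to ensure that the groups are comparable despite the cluster randomization".
- **Use of the check (Section 4.1).** "If significant baseline differences are detected, they will be explicitly reported and considered potential confounding variables during the interpretation of results". The sentence closes by "acknowledging that parametric adjustment methods may not be applicable given the sample size constraints".
- **General rule on methods (Section 2.10).** After a Shapiro–Wilk test, "the use of non-parametric statistics is assumed to be a priority, unless the data demonstrates a normal distribution".

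Section 2.10 also says that the article is the complete analysis plan and that no separate one exists, so an adjusted analysis has not been deferred to another document. The same section makes estimating the size of the effect the main statistical goal and promises effect sizes with 95% CIs, without naming the measure.

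**The concern.** Two intact practice shifts are compared on a gain score. Subtracting the pre-test uses the baseline, but with its coefficient set at 1. If the true slope of post-test on pre-test is below 1 and the shifts differ by chance at baseline, the lower-scoring shift tends to gain more for reasons unrelated to the intervention.

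The plan's safeguard is a significance test on 38 students, and imbalance is carried into the interpretation only if that test is significant. A moderate imbalance would usually pass unflagged, and a non-significant result would be read as evidence that the shifts are alike. The one remedy that uses data already collected, a model with Form 0 as covariate, is set aside on grounds of size.

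What is at stake is the precision and the interpretation of an effect estimate meant to inform a later trial.

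**Working it through.** The article states no power, effect size, SD, pre-post correlation or intracluster correlation, so there is no figure to reproduce. From the article: 18 + 20 = 38 students, one cluster per arm, significance level 0.05 (two-sided assumed). Assumed: pre-post correlation ρ = 0.3, 0.5, 0.7; ratio k = post-test SD / pre-test SD of 1.0 or 1.2; intracluster correlation 0.05 or 0.10.

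**1. Is there room for a covariate?** Intercept, arm and Form 0 use three parameters: 38 − 3 = 35 residual degrees of freedom. Adding first-year grade leaves 34.

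**2. What can the baseline check detect?** The standard error of a baseline difference is √(1/18 + 1/20) = 0.325 SD. An observed difference must reach about 0.66 SD to be significant (t approximation), so an observed 0.5 SD difference would not be flagged. Simulated Mann–Whitney power at 18 vs 20 (10,000 runs):

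| True imbalance (SD) | Probability of detection |
|---|---|
| 0.3 | 0.14 |
| 0.5 | 0.31 |
| 0.8 | 0.64 |

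**3. Variance, adjusted model against gain score.** Ratio = k²(1 − ρ²) / (1 + k² − 2ρk), which is (1 + ρ)/2 when k = 1. Multiply by 1 + 1/(38 − 4) = 1.029 for estimating the slope.

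| ρ | k = 1.0 | after slope cost | k = 1.2 | after slope cost |
|---|---|---|---|---|
| 0.3 | 0.65 | 0.669 | 0.762 | 0.784 |
| 0.5 | 0.75 | 0.772 | 0.871 | 0.897 |
| 0.7 | 0.85 | 0.875 | 0.966 | 0.995 |

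With equal SDs the saving is about 33%, 23% and 13%. With k = 1.2 it is about 22%, 10% and nil. With equal SDs it also disappears near ρ = 0.95 (0.975 × 1.029 = 1.00).

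**4. Bias, two mechanisms, baseline difference 0.5 SD, k = 1, no intervention effect.**

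- *Chance imbalance that regresses to the mean.* Gain-score bias is −(1 − ρ) × 0.5, that is −0.35, −0.25 and −0.15 SD at ρ = 0.3, 0.5 and 0.7. Simulated at ρ = 0.5: gain score −0.26, adjusted −0.01.
- *Stable difference between the shifts.* The result reverses. Simulated at ρ = 0.5: gain score 0.00, adjusted +0.26, with type I error 0.136 for the adjusted model against 0.049 for Mann–Whitney on LG.

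**5. Cluster effects, no intervention effect, ρ = 0.5.** Type I error, Mann–Whitney on LG vs adjusted model, by the correlation between a shift's pre- and post-test effects:

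| Intracluster correlation | 0 | 0.5 | 1 |
|---|---|---|---|
| 0.05 | 0.24 vs 0.21 | 0.15 vs 0.16 | 0.05 vs 0.07 |
| 0.10 | 0.37 vs 0.33 | 0.24 vs 0.25 | 0.05 vs 0.11 |

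At a correlation of 1 the adjusted estimate has 1.03 to 1.34 times the variance of the gain score. Neither analysis is protected against cluster effects.

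**The case against.** The strongest objection is that adjustment is not a general improvement in this design. Each arm is one shift formed by enrolment. If the shifts differ stably, the gain score is unbiased and the adjusted model is not (step 4), and the article cannot tell us which case applies. This stands. A reader might infer that adjusting for Form 0 reduces bias and variance at no cost and should replace the planned comparison. The documents do not support that: the benefit depends on a mechanism, an SD ratio and a correlation that they do not give.

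The article is also candid. Sections 2.10 and 4.1 call the inference exploratory and admit cluster confounding whatever the baseline check shows. Section 4.1 hedges, saying only that adjustment may not be applicable. This softens the point, but the reason offered is still size, and size is not an obstacle.

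Two further inferences go too far:

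- *That a rank test leaves the next trial without a usable scale.* Section 2.10 promises effect sizes and 95% CIs, Section 2.4 promises a variance, and LG is on a 0 to 10 scale. Only the effect measure is left unnamed.
- *That Shapiro–Wilk will choose the primary test.* Section 2.10 names Mann–Whitney outright for the primary hypothesis, and the normality clause is a general statement. The two need reconciling, but no switch of the primary test is clearly planned.

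**Conclusion.** The point holds in a limited form and is worth acting on. Two statements should not stand: that a significance check can establish comparability, when it misses a true 0.5 SD imbalance about 69% of the time (1 − 0.31), and that sample size may rule out adjustment, when 35 residual degrees of freedom remain. The first rests on the simulated power at 18 vs 20, the second on arithmetic alone.

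The likely precision gain, about 13% to 33% of the variance, depends on equal SDs, correlations of 0.3 to 0.7 and no cluster effects. It falls to nothing under other plausible values. The direction of any bias correction depends on whether a baseline difference is chance or stable. The evidence therefore supports adding an adjusted estimate beside the gain-score difference. It does not support making the adjusted estimate the sole primary result, and it does not show that the planned comparison is invalid beyond the one-cluster-per-arm limitation that the article already admits.

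**What to change.** In Section 2.10:

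- Pre-specify two estimates, each with a 95% CI and reported together whatever Shapiro–Wilk or any baseline comparison shows: the unadjusted difference in mean global LG, and the arm coefficient from a linear model of global LG on arm and Form 0 score, with first-year grade as an optional second covariate.
- Keep Mann–Whitney, with the Hodges–Lehmann shift, as a sensitivity analysis, and align the normality clause with this.
- Replace the baseline p-values with standardized differences, and delete the claim that the check ensures comparability.

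In Section 4.1:

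- Delete the sample-size reason against adjustment, and stop making discussion of imbalance depend on significance.
- Keep the one-cluster caveat and extend it: neither estimate, nor its participant-level CI, separates the intervention from the shift.
- State that the two estimates can differ because one suits chance imbalance and the other a stable shift difference.

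No new data are needed, since Form 0 and grades are already collected. The adjusted model costs one degree of freedom (about 3% in variance), or two with grade. It also assumes a linear slope and may be biased if the shifts differ stably, which is why both estimates are shown.
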